# SYNOPSIS

| **Protocol Title** | First line surgery versus first line fertility treatment using assisted reproductive technologies in patients with advanced endometriosis: A national multicenter randomized controlled trial. |
| --- | --- |
| **Indication** | Patients with endometriosis AAGL stage III-IV eligible for their first fertility treatment |
| **Primary objective** | To assess whether surgery conducted prior to treatment with assisted reproductive technologies (ART) in patients with endometriosis AAGL stage III-IV increases cumulative live birth (CLBR) as compared to first line ART. |
| **Secondary**  **objectives** | To assess if surgery prior to ART treatments in women with endometriosis AAGL stage III-IV result in improved, Cumulative Pregnancy Rate (CPR) and lower miscarriage rate as compared to first line ART.  To compare time to CLBR and CPR  To evaluate intra- and postoperative complications after oocyte pick-up and surgery.  To compare quality of life and pain at follow up and do a health economic evaluation.  To examine obstetrical outcomes of the resulting pregnancies  To investigate differences in plasma progesterone levels (P-progesterone) at the day of frozen embryo transfer in hormone replacement therapy (HRT) cycles |
| **Study Design** | Randomized controlled trial |
| **Planned sample**  **Size** | 350 |
| **Inclusion criteria** | - Age 18 - 38 years. - Endometriosis AAGL stage III-IV - Eligible for ART-treatment such as in vitro fertilization (IVF) or intracytoplasmic sperm injection (ICSI) - Body mass index 18 – 35 kg/m^2^ |
| **Exclusion criteria** | - Previous surgery for endometriosis except diagnostic laparoscopy. - Previous IVF/ICSI cycles - Hemato- /hydrosalpinx - Clear indication for surgery such as ureteral stenosis or intestinal sub-occlusive symptoms - Suspicion of ovarian malignancy - Submucosal fibroids of any size (FIGO 0-1) or intramural fibroids (FIGO 2-5) > 4 cm - Uterine malformations (U 1-6 according to ESHRE classification) - Contraindications to surgery - ART treatment with donated oocytes |
| **Primary outcome** | Cumulative live-birth rate (CLBR) within three years from first treatment (Surgery or ART) |
| **Secondary**  **outcomes** | - Cumulative Pregnancy Rate (CPR) - Time to pregnancy and live birth - Miscarriage rate - Reproductive outcomes per IVF cycle, - Rate of recurrent implantation failure (RIF) - Intra- and postoperative complications after surgery - Infections after oocyte pick-up - Quality of life - Pain - Health costs - Obstetrical outcomes and complications - P-progesterone at the day of frozen embryo transfer in HRT cycles |
| **Standard treatment** | First line ART |
| **Experimental**  **Treatment** | First line surgery followed by ART |
| **Duration of study**  **including follow up** | 6 years (inclusion 3 years and follow-up 3 years) |

# LIST OF ABBREVIATIONS

AAGL American Association of Gynecologic Laparoscopists

ADL activity of daily life

AMH anti-mullerian hormone

ART assisted reproductive technologies

ASA-class The American Society of Anesthesiologists physical status classification system

BMI body mass index

COS controlled ovarian stimulation

CPR cumulative pregnancy rate

CLBR cumulative live birth rate

DSMB Data Safety Monitoring Board

DE deep endometriosis

DET double embryo transfer

eCRF electronic Case Report Form

EHP-30 Endometriosis Health Profile

ESHRE European Society of Human Reproduction and Embryology

ET embryo tranfer

FET frozen embryo transfer

rFSH recombinant follicle stimulating hormone

FIGO The International Federation of Gynecology and Obstetrics

GCP Good Clinical Practice

GnRH Gonadotropin hormone-releasing hormone

GV – germinal vesicle stage oocyte

hMG human menopausal gonadotropin

HRQoL Health related quality of life

HRT – Hormone Replacement Therapy

ICSI intracytoplasmic sperm injection

IDEA International Deep Endometriosis Analysis group

IVF in vitro fertilization

KVÅ klassifikation av vårdåtgärder

LBR live birth rate

MI metaphase I oocyte

MII metaphase II (mature) oocyte

MFR Swedish Medical Birth Register

MUSA Morphological Uterus Sonographic Assessment

MRI magnetic resonance imaging

NC natural cycle

NRS Numeric Rating Scale

OHSS ovarian hyperstimulation syndrome

OPU oocyte pick up

PR pregnancy rate

QALYs quality-adjusted life years

Q-IVF National Quality Registry for Assisted Reproduction

rASRM revised American Society for Reproductive Medicine classification of endometriosis

RCTs randomized controlled trials

RedCap Research Electronic Data Capture system

RIF Recurrent Implantation Failure

SET single embryo transfer

# WHY THIS TRIAL IS NEEDED

BACKGROUND

Endometriosis

Endometriosis is a prevalent condition affecting 10% of female population of reproductive age, leading to pain and subfertility (1). An earlier systematic literature review and meta-analysis suggests that women with advanced endometriosis (revised American Society for Reproductive Medicine classification of endometriosis (rASRM) stage III-IV) have a lower likelihood of achieving clinical pregnancy/live birth compared to women without endometriosis, while this difference has not been observed for mild disease (stage I-II) (2).

Gynecological Ultrasound and staging

The prevalence of endometrioma and deep endometriosis found through systematic transvaginal ultrasound on women referred for ART treatment in Sweden has been estimated at 21.8% (3). Additionally, 75.8% of those with endometriosis were unaware of their condition prior to diagnosis (3). In recent years, two staging systems, namely the American Association of Gynecologic Laparoscopists (AAGL) Endometriosis classification (4, 5) and #ENZIAN (6) have gained prominence owing to their accuracy when juxtaposed with surgical findings.

Surgical Treatment

Women with endometriosis seem to experience pain relief after bowel surgery due to endometriosis (7, 8). Consensus from the European Society of Human Reproduction and Embryology (ESHRE) indicates that surgery can be performed prior to treatment with assisted reproductive technologies (ART) (7). Additionally, the number of spontaneous pregnancies is high after surgery on patients with deep endometriosis (10). Furthermore, in patients with endometriosis stage I-II or in infertile patients with endometriomas, surgery can in some cases be considered to improve fertility (7-9). However, the risk of severe complications in patients undergoing rectal surgery is up to 10% including anastomosis leakage and fistulas (10, 11).

Fertility treatment

An earlier meta-analysis found that the number of oocytes and fertilization rates are lower in women with endometriosis as compared to those without, although not necessarily impacting the live birth rate (12). Still, some previous studies have shown lower likelihood of live birth and pregnancy after in vitro fertilization (IVF) in women with endometriosis compared to women with unexplained or tubal infertility (13, 14). Even though there is some controversy when it comes to the evidence of association between endometriosis and adverse reproductive outcome after IVF, there is biological plausibility for this type of association, especially in women with advanced endometriosis (chronic inflammation affecting folliculogenesis, technical difficulties at oocyte retrieval due to endometriomas or adhesions, increased risk of pelvic infection after oocyte pick-up) (15, 16).

RATIONALE FOR STUDY

Only a few comparative retrospective studies on first-line surgery versus first-line ART have been performed, with no available randomized controlled trials (RCTs) (17). In two retrospective register studies, first-line surgery in patients with deep endometriosis (DE) in the anterior compartment or colorectal DE showed improved live birth rates (LBR) and pregnancy rates (PR) compared to first-line ART (18, 19). An important limitation in the previous studies on patients with endometriosis has been the challenge of staging and characterizing the disease consistently using preoperative imaging techniques. Currently, the decision regarding the choice between surgery and IVF is collaborative and individualized, considering various factors such as the patient's medical and surgical history, presence of pain symptoms, age, results of ovarian reserve testing, and semen analysis. Lack of randomized RCTs or at least robust prospective cohort studies comparing these two approaches is noteworthy. Hence, there is an obvious need for a randomized controlled trial to address the impact of surgery prior to ART on the reproductive outcomes in women with endometriosis AAGL stage III-IV, to help patients and health-care workers with decision-making, with the overall aim to improve patient-outcomes.

# STUDY OBJECTIVES

HYPOTHESIS

First line surgery (prior to ART treatment) in women with endometriosis AAGL stage III-IV will result in improved cumulative live birth rate (CLBR) as compared to first line ART.

PRIMARY OBJECTIVE

To assess whether surgery conducted prior to ART in women with endometriosis AAGL stage III-IV increases chances of CLBR as compared to first line ART.

.

SECONDARY OBJECTIVES

To evaluate whether surgery prior to ART treatments in women with endometriosis AAGL stage III-IV will result in improved cumulative pregnancy rate (CPR) and lower miscarriage rate as compared to first line ART.

To compare whether surgery prior to ART treatments in women with endometriosis AAGL stage III-IV will result in shorter time to live birth or pregnancy as compared to first line ART.

To investigate if surgery prior to ART treatments in women with endometriosis AAGL stage III-IV will result in better reproductive outcomes per IVF cycle and a lower rate of recurrent implantation failure (RIF).

To assess if surgery prior to ART treatments in women with endometriosis AAGL stage III-IV will result in lower rate of infections after oocyte pick-up requiring treatment with antibiotics as compared to first line ART?

To evaluate if surgery prior to ART treatments in women with endometriosis AAGL stage III-IV result in higher Quality of life and less pain measured with Endometriosis Health Profile (EHP-30) and Numeric Rating Scale (NRS) before ART, i) at the time of oocyte retrieval, ii) two months after ART and iii) at the three-year follow-up visit as compared to first line ART.

To explore whether surgery prior to ART treatments in women with endometriosis AAGL stage III-IV will be cost effective compared with first line ART?

To examine if surgery prior to ART treatments in women with endometriosis AAGL stage III-IV will result in reduced pregnancy and delivery complications, as well as fewer complications within 8 weeks postpartum, compared to first line ART.

To investigate whether serum progesterone level on the day of frozen embryotransfer in hormone replacement cycles in patients with severe endometriosis is associated with reproductive outcomes (LBR, pregnancy rate, miscarriage rate) and to determine if there is any difference in p-progesterone level between the two different study groups first line ART vs first line surgery in women with endometriosis AAGL stage III-IV?

PRIMARY OUTCOME MEASURE

Cumulative live-birth rate within three years from first treatment (surgery or ART treatment).

Definition of primary outcome measure

CLBR is defined as any live births from first treatment until end of follow up (three years from first ART treatment or surgery or drop out from the study, whichever comes first).

Primary outcome will be calculated considering also the following pre-specified subgroups: study center,  type of ART-treatment (IVF or ICSI), age (< and > 35 years), ovarian reserve ( anti-mullerian hormone (AMH) <0.5ng/L, 0.5-3.5 ng/L and AMH >3.5ng/L ) (35) adnexal surgery (yes/no), surgery on deep endometriosis anterior compartment (yes/no) or deep endometriosis posterior compartment (yes/no) (defined by Classification of surgery, “Klassifikation av vårdåtgärder” (KVÅ codes), see appendix).

SECONDARY OUTCOME MEASURE

- Cumulative Pregnancy Rate (CPR)
- Time to pregnancy and live birth
- Spontaneous Pregnancy Rate
- Miscarriage rate and/or extrauterine pregnancies
- Reproductive outcomes per IVF cycle
- Rate of recurrent implantation failure (RIF), (20) evaluated at the end of the study period
- Infections after oocyte pick-up
- Quality of life and pain
- Peri- and two months postoperative complications classified by Clavien-Dindo and Classic systems
- Health care costs
- Obstetrical outcomes and complications
- P-progesterone levels on day of embryo transfer at first HRT frozen-thawed artificial embryo transfer cycle

Definition of secondary outcome measures

Cumulative Pregnancy Rate (CPR) is defined as all pregnancies confirmed with ultrasound, from first treatment (surgery or ART) until three years of follow up.

Time to pregnancy is defined as time from first treatment (surgery or ART) to first pregnancy confirmed with ultrasound. Time to live birth defined as time from first treatment (surgery or ART) to first livebirth.

Spontaneous pregnancy rate is defined as any spontaneous pregnancy occurring between first treatment and end of follow-up.

Miscarriage rate defined as frequency and proportion of spontaneous loss of any clinical and biochemical pregnancy before week 22 and/or extrauterine pregnancy defined as a pregnancy not located in the uterine cavity, occurring between first treatment and end of follow-up.

Reproductive outcome per IVF/ICSI-cycle: number of oocytes retrieved (mature and/or total), fertilization rate, Fresh embryo transfer (ET) (day 2, day 3, day 5), number of blastocysts cryopreserved, pregnancy rate per ET, live birth rate per ET, miscarriage rate per ET, cumulative pregnancy rate per cycle, cumulative miscarriage rate per cycle, cumulative live birth rate per cycle.

RIF (recurrent implantation failure) evaluated at the end of the study period. RIF is defined here as no pregnancy after three ETs in women <35 years and four ETs in women 35-39 years old (20).

Infections after oocyte pick-up will be registered yes/no and further classified as requiring i) treatment with antibiotics, ii) readmission or iii) surgical intervention.

Health related quality of life (HRQoL) and pain will be assessed by questionnaires, Endometriosis Health Profile (EHP-30), EQ5D and Numeric Rating Scale (NRS), completed by study participants preferably as electronical patient reported outcome measures or during the clinic visit (by manually filling in forms, by accessible computer or by mail). The assessments are performed maximum one month before the first intervention, at the time of oocyte retrieval, two months after ART or surgery and at three-year follow-up.

Intraoperative complications will be classified by Classic systems (21).

Two months postoperative complications will be defined according to the Clavien-Dindo (22) system.

Health care costs from randomization to end of trial: Direct costs will be used by assessing internal accounting and billing systems within the hospitals, cost per patient (CPP). We will also measure the quality-adjusted life years (QALYs) gained with the intervention and use this to undertake a cost-utility analysis. The QALY calculations will be based on fertility status measures for trial participants, with valuations of changes in fertility status and quality of life based on the EQ-5D.

Obstetrical outcomes and complications defined as:

- pregnancy- related complications: premature delivery, preeclampsia, gestational diabetes, placenta previa, placenta ablation, placenta spectrum disorders
- delivery-related complications: emergency caesarean section, pelvic floor trauma, delivery related bleeding, manual placenta removal
- postpartum complications (defined as within 8 weeks postpartum): infections (endometritis, pelvic inflammatory disease, urinary tract infection, wound infection, sepsis), remaining conceptual tissue with and without surgical intervention, use of analgesics

COVARIATES

Potential covariates will be collected from patients’ medical records.

*Baseline characteristics:*

- Age (continuous and dichotomized as < and > 35 years)
- Infertility duration (months)
- Infertility due to social factors (yes/no)
- Infertility due to pain from endometriosis (yes/no)
- Infertility due to male factor (yes/no)
- Smoking (yes/no)
- Snuffing (yes/no)
- BMI (continuous)
- Hormonal endometriosis treatment (yes/no, if yes subtype of drug, duration of hormonal treatment prior to first surgery or ART)
- Parity (0, 1-2 or >2)
- previous caesarian sections (yes/no)
- previous abdominal surgery (yes/no)
- previous adnexal surgery (yes/no)
- previous uterine or cervical surgery (yes/no, type of surgery)
- smoking habits (yes/no)
- ovarian reserve (AMH<0.5ng/L, 0.5-3.5 ng/L and AMH >3.5ng/L)
- myoma (yes/no)
- time from randomization to first oocyte pick-up or surgery (depending on which treatment arm the patient is randomized to)
- ASA-class (1-2 or 3-4)
- Other diseases affecting the outcome: hypothyroidism, diabetes, bleeding disorders or thrombogenic diseases, hypertension, hyperprolactinemia

*Imaging specific data (Ultrasound MRI)*:

- #ENZIAN-score
- AAGL-score
- Adenomyosis (yes/no)
- antral follicle count (AFC)

*Perioperative data:*

- #ENZIAN score
- AAGL score
- EFI score
- Surgical procedure defined by KVÅ- codes: adnexal surgery (yes/no), surgery on deep endometriosis anterior compartment (yes/no) or deep endometriosis posterior compartment (yes/no)
- Colorectal surgery (yes/no, if yes rectal shaving, discoid resection or segmental resection)
- Urological surgery (yes/no, if yes bladder resection, reimplantation of ureter, end to end anastomose of ureter, shaving of ureter)
- Perioperative data: estimated blood loss, operative time, conversion rate
- Annual surgeon volume (number of advanced endometriosis surgeries per year)
- Cumulative surgeon volume (number of advance endometriosis surgeries in total at surgery)
- Consultant surgeon (yes/no, if yes which specialty)
- Reoperation (yes/no) until 2 months post-surgery
- Readmissions (yes/no) until 2 months post-surgery
- Hospital stays (days)
- Time to normal activity of daily life (ADL) (days)

*Assisted reproductive technologies data (for each IVF/ICSI-cycle, max 3):*

- Complication – yes/no
- Type of complication (infection, ovarian hyperstimulation syndrome (OHSS), bleeding)
- Time from surgery to first oocyte pick-up
- Type of IVF protocols (GnRH agonist protocol/GnRH antagonist protocol)
- Total dose/mean daily dose of follicle stimulating hormone (rFSH) /human menopausal gonadotropin (hMG)
- Duration of IVF stimulation (days)
- Cancelled cycle (before or after oocyte pick up (OPU)) (excluding freeze all cycles)
- Reason of cancelled cycle
- Type of ovulation triggering [GnRH agonist (Gonapeptyl/Suprecur/Suprefact/Synarela) / Ovitrelle]
- Date of OPU
- Freeze all cycle (yes/no) and reason of that
- Number of retrieved oocytes (GV/MI/MII)
- Performed fertilisation method (ICSI/IVF)
- Sperm – fresh vs frozen
- Donor sperm – yes/no
- Origin of sperm – ejaculated/ epidydimal / testicular
- Oocytes – fresh vs frozen
- Number of inseminated oocytes
- Number of fertilised oocytes
- Number of good quality embryos defined according to Gardner criteria as AA, AB and BB for blastocysts (23) or top and good quality based on the number of blastomeres, the fragmentation rate and the multinucleation of blastomeres for cleavage stage embryos (24).
- Number of frozen blastocysts (D5 or D6)
- Date for fresh embryo transfer
- Embryo age at fresh embryo transfer (D2, D3, D4, D5 or D6)
- Number of embryos transferred (SET/DET)
- Type of embryo transfer (Fresh/Frozen)
- Type of protocols for Frozen-thawed ET (Natural Cycle (NC), HRT, Letrozol-stimulated, gonadotropinstimulated)
- Use of GnRH downregulation in Frozen-thawed HRT cycle (yes/no, number of days)
- Total estrogen dose and type of estrogen preparations in HRT FET-cycle
- Endometrial thickness prior to embryo transfer in HRT-FET
- Cycle day of endometrial thickness measurement in HRT-FET
- P progesterone level on the day of ET in HRT-FET
- Date of frozen ET
- Urinary pregnancy test (positive/negative)
- Gestational age at pregnancy ultrasound
- Fetal heartbeat at ultrasound (present/absent)
- Number of foetuses
- Number of gestational sacs
- Result foetus 1 (miscarriage, abortion, ectopic pregnancy, delivery)
- Date for delivery / end of pregnancy foetus 1
- Result foetus 2 (miscarriage, abortion, ectopic pregnancy, delivery)
- Date for delivery / end of pregnancy foetus 2
- Result foetus 3 (miscarriage, abortion, ectopic pregnancy, delivery)
- Date for delivery / end of pregnancy foetus 3

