# STUDY TREATMENT

Time from randomization to first treatment (surgery or first ART cycle) should be minimized with a goal of three months and should preferably not exceed six months. Complications due to treatments (IVF or surgery) will be register in the eCRF and treated according to clinical routine at each hospital.

EXPERIMENTAL TREATMENT

First line endometriosis surgery followed by ART such as IVF or ICSI.

STANDARD/CONTROL TREATMENT

First line ART such as IVF or ICSI.

SURGICAL PROCEDURE

Surgery will be performed at one of four nationally specialized centers in advanced endometriosis surgery (Södersjukhuset Stockholm, Sahlgrenska University Hospital Göteborg, Skånes University Hospital, Malmö/Lund, Uppsala University Hospital). Intraoperative AAGL endometriosis staging, #ENZIAN classification and Endometriosis Fertility Index (EFI) (31) will be recorded in the study protocol. Surgery will be conducted according to the ESHRE recommendations of surgery in endometriomas and deep endometriosis (32, 33). Surgery should be multidisciplinary when needed (colorectal surgeons and urologists). The goal of the procedure is to remove as many endometriotic lesions as possible while also minimizing negative impact on organ function, since endometriosis is a benign disease. Rectal endometriosis will be removed with rectal shaving, discoid or segmental resection depending on the size and placement of the lesion in the rectal wall. Laparoscopic cyst enucleation is considered the "golden standard" as it is associated with a low recurrence rate, significant pain relief, and increased chances of spontaneous conception (34). In cases where ovarian reserve is already diminished, more gentle methods such as ablation therapy with CO2 Laser/Plasma Jet or sclerotherapy could be employed (35-37). These methods can also be used in combination with conventional surgical cyst enucleation. The choice of surgical technique should be tailored to the individual patient's needs.

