# PATIENT REPORTED OUTCOMES (PROMS)

When evaluating quality of life among women with endometriosis many different scales have been used, mostly of generic character that are not specific to the disease. One of these is 30-item Endometriosis Health Profile (EHP30), a scale that perform well in clinical practice in the routine evaluation of Health-Related Quality of life (HRQoL) The use of EHP30 is recommended by the National Board and Welfare in Sweden, the ASRM and ESHRE (40). Using EHP-30, a small study has shown an improvement in HRQoL in the follow-up after endometriosis surgery, an effect that may last for up to 6.8 years (41). Two recent studies show postoperative improvement in HQQoL measured by EHP-30 10 weeks and 3 months after surgery, respectively (42, 43). Especially women with deep endometriosis (DE) showed a more significant benefit from surgery (43). However, HRQoL can also be affected by infertility, and in this trial, infertility treatment will be delayed, thus, HRQoL is an important measurement.

POINTS OF ASSESSMENT

Baseline assessment will be obtained after randomization and maximum 1 month prior to surgery or start of first ART cycle

Thereafter assessment will be done prospectively at:

- 2 months after surgery (for the group randomized to first line surgery)
- 1:st oocyte pick up (for both randomization groups)
- 2 months after 1:st oocyte pick up
- 2:nd oocyte pick up
- 2 months after 2:nd oocyte pick up
- 3:rd oocyte pick up
- 2 months after 3:rd oocyte pick up
- Visit, phone call or questionnaire 3 years after randomization.

Compliance with completing the questionnaires will be investigated at each time point to

evaluate the procedure for data collection and the feasibility of the questionnaires.

INSTRUMENTS

The core questionnaire in EHP -30 includes 30 questions in 5 health-related areas: pain, control and powerlessness, emotional well-being, social support, and self-image. In addition, there are six supplementary modules covering work, relationship with child/children, sexual relationship, feelings about the medical profession, feelings about treatment and feelings about infertility.

The Numeric Rating Scale (NRS) is a frequently utilized pain assessment tool commonly employed in postoperative care. It allows for the momentary evaluation of pain on a scale from 0 to 10, with 0 representing "no pain" and 10 indicating "the worst pain imaginable”.

EQ-5D is a standardized non-disease specific instrument for describing and

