# STATISTICAL CONSIDERATIONS

The primary exposure is the randomized allocation (surgery prior to ART vs ART alone). All analyses will follow the intention-to-treat (ITT) principle, meaning participants are analyzed according to their randomized group regardless of adherence. Per-protocol and as-treated analyses will be conducted as sensitivity analyses to assess robustness. An interim analysis at the halfway point is planned to monitor potential adverse effects and ensure the safety of the interventions.

No formal adjustment for multiplicity will be made; the primary endpoint will be tested at a two-sided α=0.05, while secondary endpoints are considered supportive and exploratory. Sensitivity analyses will address protocol deviations, handling of missing data, and robustness to alternative modelling approaches.

DATA ANALYSES

Baseline demographic and patient’s characteristics will be summarized by treatment group. Continuous variables will be described with mean, standard deviation, median, interquartile range, minimum and maximum, and categorical variables with counts and percentages.

Primary endpoint

The primary endpoint of the study is the Cumulative Live Birth Rate (CLBR), defined as the proportion of participants achieving at least one live birth within three years following the initiation of treatment.

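### The fertility outcomes are timed from first treatment instead of randomisation, so the pre-treatment wait drops out and women never treated have no time zero

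*Protocol*

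**What the plan says.** The clock for the fertility outcomes starts at first treatment throughout the Protocol.

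- Study Objectives, primary outcome: "Cumulative live-birth rate within three years from first treatment (surgery or ART treatment". The definition below it reads "CLBR is defined as any live births from first treatment until end of follow up".
- Statistical Considerations, primary endpoint: "proportion of participants achieving at least one live birth within three years following the initiation of treatment".
- Study Objectives, secondary outcomes: "Time to pregnancy is defined as time from first treatment (surgery or ART) to first pregnancy confirmed with ultrasound". Cumulative pregnancy, time to live birth and spontaneous pregnancy start at the same point.
- Study Enrollment defines the start of the trial as the operation or the first FSH injection.

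Randomisation comes earlier. Study Treatment describes the interval to first treatment as one to be minimised, "with a goal of three months and should preferably not exceed six months". The procedure for the patient-reported outcomes says that a treatment date can be set only once the arm is known. It acknowledges that waits vary, but deals with this only for the quality-of-life baseline.

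Study Enrollment also says that women withdrawn between randomisation and treatment are replaced by new recruits. Statistical Considerations says that all analyses follow intention to treat by randomised group.

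Other parts use a different anchor. Costs are "Health care costs from randomization to end of trial". The list of questionnaire time points ends with "Visit, phone call or questionnaire 3 years after randomization", whereas the schedule of events places that same contact three years after first treatment.

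**The concern.** The trial compares two strategies, and a woman is committed to one of them at randomisation. Because treatment is scheduled after allocation, the queue is a consequence of the arm. A clock that starts when the queue ends has three effects.

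1. If the waits differ by arm, the difference vanishes from the primary proportion and from the time-to-event outcomes. The arm with the longer queue looks better than it would to a woman choosing between the strategies. One stated objective is whether operating first shortens time to pregnancy or live birth, and a measure without the queue does not answer it fully.
2. A woman who conceives while waiting, and so never starts treatment, has no time zero. Her pregnancy also lies outside the spontaneous-pregnancy window.
3. The endpoint is undefined for any randomised woman who is never treated, and some of these women are replaced. The analysed set then depends on events after allocation, which intention to treat is meant to prevent.

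**Working it through.** **Inputs from the Protocol.** Live-birth rates of 55% (ART first) and 71% (surgery first), two-sided alpha 0.05, 80% power, 142 per arm (Power Calculation and Sample Size). Waits of three to six months (Study Treatment).

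**The plan's own figure.** With the pooled normal approximation and mean rate 0.63:

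n = [1.960·√(2·0.63·0.37) + 0.842·√(0.55·0.45 + 0.71·0.29)]² / 0.16² = 141.8, so 142 per arm. Power at 142 is 80.1%. The sample-size arithmetic for 142 is not in question here.

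**Assumption.** The Protocol gives no birth curve. Assume births accrue at a constant hazard from month 9 to month 36 after first treatment and reach the planned rates at month 36:

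- ART first: h = −ln(0.45)/27 = 0.0296 per month
- Surgery first: h = −ln(0.29)/27 = 0.0458 per month

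With a horizon of H months from randomisation and a wait of w months, the rate is 1 − exp(−h·(H − w − 9)).

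**Clock at randomisation, H = 36:**

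| Wait ART / surgery (months) | ART first | Surgery first | Difference (points) | Power at 142 per arm |
|---|---|---|---|---|
| Present clock | 55.0% | 71.0% | 16.0 | 80% |
| 3 / 3 | 50.8% | 66.7% | 15.9 | 78% |
| 3 / 6 | 50.8% | 61.8% | 11.0 | 46% |
| 6 / 3 | 46.3% | 66.7% | 20.5 | 94% |

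Example for 3 / 6: ART 1 − exp(−0.0296·24) = 0.508; surgery 1 − exp(−0.0458·21) = 0.618. Differences are taken before rounding.

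**No effect once treatment starts (55% in both arms).** Waits of 3 (ART) and 6 (surgery) months give 50.82% and 46.26%, a difference of −4.56 points from randomisation. The present clock shows zero.

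**Clock at randomisation, H = 42.** Equal waits of six months return the planned 55.0% and 71.0%. Equal waits of three months give 58.8% and 74.7%, a difference of 15.9 points with 82% power. Waits of 3 / 6 give 58.8% and 71.0%, a difference of 12.2 points with 58% power. Waits of 6 / 3 give 55.0% and 74.7%, a difference of 19.7 points with 94% power.

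**Women never treated.** The Protocol gives no share. Assume 10% in the surgery arm and 5% in the ART arm, kept in the denominator:

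- None has a live birth: 0.71·0.90 − 0.55·0.95 = 0.6390 − 0.5225 = 11.65 points.
- All have one: (0.6390 + 0.10) − (0.5225 + 0.05) = 16.65 points.

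Leaving them out gives 16.0 points.

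**The case against.** The strongest reply is that this is a deliberate and mostly consistent choice. The synopsis, objectives, statistics section and monitoring charter all use first treatment, and each treated woman gets the same 36 months. That answers a recognisable question: does surgery help once care begins? One waiting target applies to both arms, and nothing shows that the waits differ. Study Enrollment also has eligibility entered about a month before treatment, which may mean short waits. With equal waits the difference hardly moves.

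Much of this stands, and it limits the point. A reader might go further in four ways that the Protocol does not support.

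- **That the clock favours surgery.** No waiting time is given by arm, and the shift reverses if ART waits longer.
- **That the delay caused by operating is hidden.** The two to three months of recovery before ART lie inside the clock, which starts at the operation. Only the queue before first treatment is lost.
- **That the rest of the Protocol already runs from randomisation.** The questionnaire list does, but the schedule of events contradicts it. That is a conflict to reconcile, and no precedent. A cost window from randomisation does not settle the fertility clock.
- **That the stated duration, "6 years (inclusion 3 years and follow-up 3 years", fits only a clock from randomisation.** It is a rounded synopsis figure, and it also fits the present clock if inclusion is counted close to treatment.

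The reply does not remove the difficulty with women never treated or with conceptions during the wait. Neither depends on unequal queues, and a consistent definition of time zero does not make it compatible with intention to treat.

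**Conclusion.** The point holds as a flaw in the definition of time zero. Its numerical effect is conditional. The present rule removes any arm difference in waiting from the primary and time-to-event outcomes, does not count women who conceive while waiting and never start treatment, and leaves randomised but untreated women without an outcome while replacing some of them.

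The bias has unknown sign and size. Under the constant-hazard assumption it is negligible with equal waits (15.9 against 16.0 points). It is about 4.5 to 5 points in either direction when one arm waits three months and the other six (11.0 or 20.5 points). These two cases set the target wait in one arm against the preferred maximum in the other, so they illustrate what the Protocol permits and do not forecast what will happen. The planning rates are described as rates after three IVF cycles, so reading them as 36-month rates is a further assumption. No rate of conception while waiting is given, so that part cannot be sized.

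**What to change.** - Make randomisation time zero for cumulative live birth, cumulative pregnancy, time to pregnancy and time to live birth, with one fixed horizon for both arms.
- Prefer 42 months. This keeps a full three-year treatment window for waits of up to six months (42 − 6 = 36). If 36 months is kept, rates and power fall: about 78% at 142 per arm with equal three-month waits, and less if surgery waits longer. The sample size should then be re-examined.
- Keep all randomised women in the denominator, including those withdrawn before treatment where consent allows. Replacement may top up recruitment but must not remove anyone from the analysis.
- Count every birth conceived after randomisation, whether or not treatment had started.
- Retain the first-treatment clock as a sensitivity analysis.
- Report waiting time by arm up to the same event that defines first treatment. The covariate list now runs to oocyte pick-up for ART, while the trial start is the first FSH injection.
- Reconcile the anchor of the three-year contact between the schedule of events (first treatment) and the questionnaire time points (randomisation).

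The change needs a protocol amendment but no new baseline data, since the wait from randomisation is already collected. With 42 months, follow-up lasts up to six months longer, and the study takes up to 3 + 3.5 = 6.5 years from first randomisation. With 36 months, the cost is the lower rates and power shown above.
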